**Interventions:**								
CBT-I		X		X	X		X	
Waitlist control (WLC)		X		X	X		X	
**Assessments:**								
*Primary outcome measures*		CBT-I	WLC		CBT-I	WLC	CBT-I	WLC
Depression severity (CES-D)		X	X		X	X	X	X
Insomnia severity (ISI)		X	X		X	X	X	X
Sleep quality (PSQI)		X	X		X	X	X	X
*Secondary outcome measures*		CBT-I	WLC		CBT-I	WLC	CBT-I	WLC
Subjective health (SF-12 Version 1)		X	X		X	X	X	X
Anxiety (HADS-A)		X	X		X	X	X	X
Treatment expectancy (modified CEQ)		X	X		X			X
Treatment acceptability (modified PARS)		X	X		X			X
Demographics	X							
Clinical comorbidity	X							
*Post-screening eligibility assessments*		CBT-I	WLC		CBT-I	WLC	CBT-I	WLC
Withdrawal criteria					X	X	X	X
Cross-condition contamination check						X		X

*CES-D* Center for Epidemiologic Studies Depression Scale, *ISI* Insomnia Severity Index, *PSQI* Pittsburgh Sleep Quality Index, *HADS-A* Hospital Anxiety and Depression Scale—Anxiety subscale, *CEQ* Credibility/Expectancy Questionnaire, *PARS* Participant Acceptability/Usability Rating Scale

### Participant timeline

Individuals interested in participating are invited to complete a two-stage screening. In stage 1 online rapid screening, they complete an online survey to review their eligibility. Those who have passed the online rapid screening will receive a link within the Qualtrics platform to sign up for the stage 2 telephone diagnostic interview screening. These telephone interviews are conducted by project assistants, who have been trained and supervised on the administration of the modified Chinese version of the CIS-R [34].

Individuals who do not meet the stage 2 telephone diagnostic interview screening eligibility criteria will receive a list of references related to insomnia and depression produced by the Department of Health and the Social Welfare Department under the Government of the Hong Kong SAR. Information regarding crisis hotlines and integrated community centers for mental wellness are provided to those currently with suicidal plans or acts, or those who have had suicidal plans or acts within the past 12 months.

Individuals who have passed the two-stage screening are directed to download proACT-S either from App Store or Google Play. Eligible participants are guided to register for their own personal accounts to enter the main study trial. They then complete the baseline assessment via proACT-S. After that, they are randomly assigned in a 1:1 ratio either to CBT-I condition or waitlist control condition.

Participants in the CBT-I condition start the 6-week CBT-I immediately after randomization, complete the post-intervention assessment right after they finish the treatment, and complete the follow-up assessment 6 weeks after the post-intervention assessment. Participants in the waitlist control group wait for 6 weeks without the proACT-S intervention and then complete the post-intervention assessment 6 weeks after the baseline assessment. The waitlist control participants start CBT-I (equivalent to that of the CBT-I group) immediately after completing the post-intervention assessment, and they complete the follow-up assessment right after finishing the 6-week CBT-I.

Emails and WhatsApp reminders are sent to participants to increase their engagement and to enhance treatment compliance. Upon completion of the study, each eligible participant receive cash coupons of HKD $100 as a token of appreciation for their participation. The proposed flow of participants is displayed in Fig. 2.

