##### Clinical comorbidity

The number of participants with a current diagnosis of four major comorbidities (generalized anxiety disorder, phobias, obsessive-compulsive disorder, and panic disorder) are estimated from the modified Chinese version of the CIS-R [34] administered in the stage 2 telephone diagnostic interview screening. The modified Chinese version of the CIS-R [34] measures the ICD-10 diagnoses related to generalized anxiety disorder (F41.1), phobias (F40.00, F40.01, F40.1, F40.2), obsessive-compulsive disorder (F42), and panic disorder (F41.0).

Primary outcome assessments take place at baseline, post-intervention, and 6-week follow-up for both CBT-I and waitlist control conditions. The schedule of enrolment, interventions, and assessments is summarized in Table 2.

**Table 2 Tab2:** The Schedule of Enrolment, Interventions, and Assessments

	Screening	Baseline		Allocation	Post intervention		6-week follow-up	
Timepoint (week)	− 12	0		1	7		13	

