### Allocation

One week following the completion of the baseline assessment, participants are randomly assigned in a ratio of 1:1 either to the CBT-I group or the waitlist control group using an online randomized algorithm (https://www.php.net/manual/en/function.random-int.php). The group assignment follows the simple randomization procedure and is completely automated to ensure allocation concealment.

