### Data analysis plan

The principle of intention-to-treat analysis will be adopted, in which all randomized participants with missing observations, from lost to follow-up or incomplete outcome assessments, will be handled by multiple imputation [53]. Missing data is assumed to be 5%.

Chi-square tests and independent *t* tests will be conducted to examine if participants in the CBT-I and waitlist control conditions differ in terms of demographic characteristics, clinical comorbidity, and baseline outcome scores. Multilevel linear mixed model based on the intention-to-treat principle will be used to calculate between-condition mean differences in the primary outcome changes in sleep quality, insomnia, and depression severity from baseline to post-intervention assessments. Multilevel linear mixed model based on the intention-to-treat principle will also be used to analyze secondary outcomes of the baseline to post-intervention change in subjective health and anxiety between CBT-I and waitlist control conditions. Clustering effect, significant baseline differences in demographics, clinical characteristics, and outcome variables will be adjusted for. Pair-sample *t* tests based on the intention-to-treat principle will be used to analyze changes in primary outcomes, subjective health, and anxiety obtained at post-intervention and 6-week follow-up separately for each condition. All comparisons are planned with a 5% two-sided significance level. Bonferroni adjustment will be applied.

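### The waitlist arm's post-intervention assessment is timed in two incompatible ways: week 6 in the Participant timeline, week 7 in Table 2

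*Protocol article*

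**What the plan says.** Four places in the protocol article fix the timing.

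- **Allocation:** "One week following the completion of the baseline assessment, participants are randomly assigned in a ratio of 1:1". Table 2 agrees, with baseline at week 0 and allocation at week 1.
- **Participant timeline, CBT-I arm:** participants "start the 6-week CBT-I immediately after randomization, complete the post-intervention assessment right after they finish the treatment". Their follow-up comes six weeks after that assessment.
- **Participant timeline, waitlist arm:** participants "wait for 6 weeks without the proACT-S intervention and then complete the post-intervention assessment 6 weeks after the baseline assessment". They then begin CBT-I at once, and "they complete the follow-up assessment right after finishing the 6-week CBT-I".
- **Table 2:** one post-intervention timepoint (week 7) and one follow-up timepoint (week 13). Each is divided into CBT-I and waitlist sub-columns, so the same week applies to both arms.

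The Data analysis plan defines the primary contrast as "between-condition mean differences in the primary outcome changes in sleep quality, insomnia, and depression severity from baseline to post-intervention assessments".

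**The concern.** The primary analysis compares change over a period that should be the same length in both arms. On the Participant timeline's wording, the CBT-I clock starts at allocation and the waitlist clock starts at baseline, one week earlier. The control arm would then be assessed a week sooner.

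Any change that happens without treatment during that extra week, in either direction, would count in the CBT-I arm but not in the control arm. Randomization does not balance this, because the offset is created by the arm itself. A model with only a categorical visit factor does not see it, because both assessments carry the same visit label. It would also be present if every CBT-I participant finished exactly on time. The Discussion expects outside events (social unrest, the pandemic) to affect outcomes, which is a further reason to observe both arms for the same time.

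Even if no bias arose, a reader of the protocol cannot tell when the control arm's primary endpoint is measured.

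**Working it through.** **Inputs**

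- Baseline to allocation: 1 week (Allocation section; Table 2).
- Allocation to start of CBT-I: none (Participant timeline).
- Length of CBT-I: 6 weeks, assessed directly afterwards (Participant timeline).
- Waitlist post-intervention assessment: 6 weeks counted from baseline (Participant timeline).
- Waitlist follow-up: directly after a 6-week CBT-I that starts at the post-intervention assessment (Participant timeline).
- Table 2: post-intervention week 7, follow-up week 13, both arms.

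**Table 2's figure, CBT-I arm**

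Post-intervention = 0 + 1 + 6 = week 7. Follow-up = 7 + 6 = week 13. Both reproduce Table 2.

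**Waitlist arm as the Participant timeline words it**

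Post-intervention = 0 + 6 = week 6. Follow-up = 6 + 6 = week 12. Each is one week earlier than Table 2. Time from allocation to the post-intervention assessment = 6 − 1 = 5 weeks, so a six-week wait fits only if it is counted from baseline, before the participant has been assigned to the waitlist.

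**Waitlist arm if the six weeks run from allocation**

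Post-intervention = 1 + 6 = week 7. Follow-up = 7 + 6 = week 13. Both match Table 2 and the CBT-I arm.

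| | CBT-I | Waitlist, Participant timeline | Waitlist, from allocation | Table 2 |
|---|---|---|---|---|
| Allocation | 1 | 1 | 1 | 1 |
| Post-intervention | 7 | 6 | 7 | 7 |
| Follow-up | 13 | 12 | 13 | 13 |

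**Completion windows**

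Under Withdrawal criteria, an assessment not completed within 2 weeks leads to withdrawal. If the window opens on the due date (an assumption), the literal windows are weeks 6 to 8 for the waitlist arm and weeks 7 to 9 for CBT-I. They share weeks 7 to 8, one week of each two-week window.

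**Sample size**

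The stated total of 199 reproduces (power 0.801 at f = 0.2 with 12 covariates), and 199 / 0.7 = 284.3, rounded up to 285, also reproduces. Neither figure depends on assessment timing.

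**The case against.** The strongest reply is that this is one misplaced word. Table 2 gives week 7 for both arms. Nobody belongs to the waitlist group until week 1, so a group member who waits six weeks reaches week 7, and only the reference to baseline at the end of the sentence points to week 6. Figures 1 and 2 are not visible and may state the timing. This stands as a plausible explanation. A reader might infer that the trial did compare week 6 with week 7; the documents do not establish that. They do not establish the contrary either. The Participant timeline's own mention of randomization following baseline gives no interval, so it does not remove the conflict.

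A reader might also infer that elapsed time is almost wholly confounded with arm. That goes too far, because the completion windows overlap for about a week and actual days since baseline can be examined. The windows do not cancel the offset in due dates, however, since they apply to both arms.

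Regression to the mean is a weak mechanism here. The severity cut-offs on the ISI and PHQ-9 are applied at stage 1 screening, which Table 2 places at week −12, so much of the regression would come before baseline. The PSQI and CES-D are not selection measures.

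The follow-up discrepancy (week 12 against 13) is not a second fault. It follows from the same phrase, and the planned follow-up tests are paired comparisons within each arm, so it does not enter a between-arm contrast.

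**Conclusion.** The inconsistency is real and follows from the protocol's own intervals. The control arm's primary assessment falls at week 6 by the Participant timeline and at week 7 by Table 2. This is a stated rule for the primary contrast, not a detail that a condensed article has left out.

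The consequence is conditional. If the Participant timeline was implemented literally, elapsed time differs by one week, 1/7 or about 14% less in the waitlist arm. If Table 2 was implemented, there is no difference and only the wording is at fault.

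Neither the size nor the direction of a bias can be derived, because the document gives no rate of change without treatment. Purely as an illustration, assume untreated improvement of 0.1 to 0.3 SD over six weeks, spread evenly. One extra week is then worth 0.1/6 = 0.017 to 0.3/6 = 0.050 SD, against a planned effect of d = 2 × 0.2 = 0.40, so 4% to 12% of it. If untreated scores worsen, the sign reverses. A reader might turn such figures into a claim of inflated type I error; that claim would rest entirely on the assumed drift. What can fairly be said is that any effect is probably modest.

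This should be fixed, but it does not by itself put the trial's conclusions in doubt.

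**What to change.** 1. Reconcile the Participant timeline, the Allocation section and Table 2 so that the post-intervention outcome assessment is counted from the same origin, allocation, in both arms and falls at the same elapsed week.
2. Before the primary analysis, check in the app's timestamps when the waitlist assessment actually opened. Assessments run through the app, so this should be on record.
3. If it opened at week 7, correct the sentence in the Participant timeline. Nothing else is needed.
4. If it opened at week 6, state that the primary contrast compares about 7 weeks with about 6, report days from baseline to post-intervention assessment by arm, and add a sensitivity analysis that uses actual elapsed time. State its limits: the completion windows overlap only in part, so the adjustment leans on the model, and elapsed time also reflects how promptly people respond. Scaling the waitlist change by 7/6 is not a good substitute, because it builds in linear change from baseline, which is the untested assumption.

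Recruitment ended on 4 September 2020, so wording, reporting and analysis are what can still change. The cost is one check of existing records, one corrected sentence and at most one sensitivity analysis on data already collected.

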### CBT-I intervention

The self-help CBT-I treatment content is based on the Chinese translated version of a well-established CBT-I treatment manual entitled “Insomnia: A Clinician’s Guide to Assessment and Treatment” [37]. CBT-I aims at changing dysfunctional cognitive beliefs and maladaptive behaviors that contribute to the maintenance of insomnia. The self-help CBT-I treatment is delivered in the Chinese language in six consecutive weekly modules via proACT-S. The duration of each module is around 45 to 60 min. The content of each treatment module is displayed in Table 1.

**Table 1 Tab1:** Content of each weekly CBT-I treatment module

Week 1	Content	Treatment overview
		Predisposing, precipitating, and perpetuating factors of insomnia
	Homework	Dysfunctional beliefs and attitudes about sleep assessment
Week 2	Content	Sleep hygiene
	Homework	Sleep hygiene assessment
Week 3	Content	Basic facts about sleep
		Relaxation therapy
	Homework	Diaphragmatic breathing relaxation (daily practice)
		Sleep diary (at least three diaries per week)
Week 4	Content	Sleep restriction
		Stimulus control
	Homework	Sleep diary (at least three diaries per week)
		Sleep restriction (sleep efficiency ≥ 90%; 15 min per week maximum)
Week 5	Content	Cognitive restructuring
		Constructive worry
		Cognitive distortions
	Homework	Thought record
Week 6	Content	Integration and review of all treatment content
		Shift work

proACT-S has been pilot tested in a sample of 32 Hong Kong Chinese participants and, later, revamped to improve user experience. One current recommendation for engaging app users was to reduce the amount of text and, instead, to use videos to deliver treatment content [38]. Therefore, animations were added to the text-based materials to enhance user experience. Following the literature recommendations [39, 40], more interactive components were incorporated into the app. In particular, proACT-S now provides (a) a clear timeline to indicate the start date for each assessment and treatment module, (b) indicators for module and assessment completion, (c) more prompts for users to follow in completing the weekly homework, (d) a modifiable sleep diary that accommodates the sleep pattern of shift-workers, and (e) individualized homework feedback.

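### The protocol gives two dates for the waitlist arm's primary assessment (week 6 in the text, week 7 in Table 2); if the text is followed, the arms are compared at unequal elapsed times.

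*Protocol article*

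**What the plan says.** Three places in the protocol article fix the timing.

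- **Allocation:** "One week following the completion of the baseline assessment, participants are randomly assigned". Table 2 agrees, with baseline at week 0 and allocation at week 1.
- **Participant timeline, CBT-I arm:** "Participants in the CBT-I condition start the 6-week CBT-I immediately after randomization", and they "complete the post-intervention assessment right after they finish the treatment". The CBT-I intervention section describes the course as "delivered in the Chinese language in six consecutive weekly modules via proACT-S".
- **Participant timeline, waitlist arm:** "Participants in the waitlist control group wait for 6 weeks without the proACT-S intervention", and they then "complete the post-intervention assessment 6 weeks after the baseline assessment".
- **Table 2:** post-intervention is at week 7 and follow-up at week 13. Each is a single timepoint spanning both arms, and all three primary outcomes are marked for both.

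The Data analysis plan makes the primary comparison the between-condition difference in change from baseline to post-intervention. Two further rules bear on timing. Under Withdrawal criteria, participants have up to two weeks to log in after assignment and up to two weeks to complete each assessment.

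**The concern.** A comparison of change scores is clean only if both arms have had the same time in which to change. Here the text and the schedule table disagree on the control arm's date, and one of the two readings gives the arms different amounts of time. Any trend in symptoms that is unrelated to treatment would then be counted partly as treatment effect, or partly against it.

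The trigger differs too. In the text, the CBT-I assessment follows an event (finishing treatment), while the waitlist assessment follows the calendar. A late start or slow progress can push the CBT-I assessment back without moving the waitlist date. A CBT-I participant who stops early never reaches the event that the text uses as the trigger. The contradiction affects all three primary outcomes, so it is more than a detail that an article would leave to a fuller document.

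**Working it through.** **Inputs.** Baseline is week 0. Randomisation is at week 1 (Allocation; Table 2). The CBT-I course lasts 6 weeks from randomisation. The wait lasts 6 weeks, with no origin stated (Participant timeline). The login and assessment windows are up to 2 weeks each (Withdrawal criteria). The design effect is Cohen's f = 0.2 (Sample size).

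**Step 1: reproduce Table 2.** CBT-I: 1 + 6 = week 7, which matches. Waitlist, if the 6-week wait is counted from allocation: 1 + 6 = week 7, which also matches.

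**Step 2: follow the text for the waitlist.** Six weeks after baseline: 0 + 6 = week 6, which does not match Table 2. Counted from randomisation, this is 6 − 1 = 5 weeks for the waitlist against 7 − 1 = 6 weeks for CBT-I.

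| Reading | CBT-I (weeks from baseline) | Waitlist | Planned gap |
|---|---|---|---|
| Participant timeline with Allocation | 7 (nominal) | 6 | 1 week |
| Table 2 | 7 | 7 | 0 |

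The follow-up date shows the same split. The waitlist follow-up comes straight after a further six-week course, so it falls at 6 + 6 = week 12 by the text and 7 + 6 = week 13 by Table 2. The Participant timeline section does not mention the one-week interval before allocation. It reads as if baseline and randomisation coincided, which may be how the mismatch arose.

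**Step 3: how far the windows could stretch the gap.** Assume that a late login delays the start of CBT-I, and so its end, by the same amount.

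- Text reading, both windows used in full: CBT-I spans week 7 to 7 + 2 + 2 = 11; waitlist spans week 6 to 6 + 2 = 8.
- Text reading, CBT-I login at the two-week limit and equal use of the assessment window: 9 against 6, or 11 against 8, a gap of 3 weeks.
- Table 2 reading, same login delay: 9 against 7, a gap of 2 weeks.

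**Step 4: illustrative size.** For two equal groups d = 2f = 2 × 0.2 = 0.40. The bias as a share of the design effect is (drift per week × weeks of gap) / 0.40. The protocol gives no drift rate, so 0.02 to 0.05 SD per week is an assumption.

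| Gap | Drift 0.02 SD/week | Drift 0.05 SD/week |
|---|---|---|
| 1 week | 0.02/0.40 = 5% | 0.05/0.40 = 12.5% |
| 3 weeks | 0.06/0.40 = 15% | 0.15/0.40 = 37.5% |

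A steeper assumed drift of 0.10 SD per week gives 0.10/0.40 = 25% for one week. The three-week row would apply to an arm's mean only if every CBT-I participant started at the limit, so it is an outer case. The sample size (199 evaluable, 285 in total) does not depend on any of this.

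**The case against.** The strongest reply is that the text clause is simply loose. Table 2 schedules both arms at week 7, and a six-week wait counted from allocation lands there too. On that reading no gap is planned. A reader might go further than the documents allow and infer that unequal timing is a settled feature of the design, so that elapsed time is confounded with treatment. The protocol does not support that; it supports a contradiction with one harmful reading.

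Other parts of the reply also carry weight.

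- **Week 7 is nominal for CBT-I, not a proven minimum.** If module 1 opens at allocation, module 6 could open at 1 + 5 = week 6, and Table 1 lists no homework for that week. Finishing could then fall between weeks 6 and 7, so the gap under the text could be less than one week for quick finishers.
- **Non-finishers may have had a date.** Table 2 gives a nominal week 7, the app is described as showing a start date for each assessment, and completion is limited to two weeks. These suggest scheduled, bounded assessments in practice. It cannot be concluded that missing data depend on adherence in one arm only. What remains is that the text ties the CBT-I assessment to finishing, and no passage says that the calendar date overrides this.
- **Regression to the mean is a tempting mechanism but a weak one.** Selection on insomnia and depression scores takes place at screening, and the outcome baseline is measured separately afterwards. Much of any regression would have occurred before baseline.
- **The direction is open.** The Discussion expects social unrest and the pandemic to affect symptoms adversely. If symptoms were worsening, a later assessment would count against CBT-I.
- **Recall periods overlap.** The insomnia measure looks back two weeks and the sleep-quality measure one month, so a one-week shift covers much of the same period.

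None of this removes the conflict between the text and the table, or the different triggers in the two arms.

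**Conclusion.** The point holds as an internal contradiction about the primary endpoint. The waitlist assessment is at week 6 by the Participant timeline section and at week 7 by Table 2, with CBT-I nominally at week 7 under both. If the text is followed as written, the primary contrast compares elapsed times that differ by about one week, and by more where CBT-I participants start late or finish slowly. If Table 2 is followed, no gap is planned, although tying the CBT-I assessment to completion could still create one.

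The bias is probably modest. Its size and direction cannot be fixed from the document. The percentages above rest on assumed drift rates and, for the larger ones, an assumed three-week lag; they show scale and are not estimates. The contradiction should be resolved before the primary analysis, because the timepoint of that analysis ought to have only one reading.

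**What to change.** Reconcile the Participant timeline section, the Allocation section and Table 2, so that the post-intervention assessment is due at the same stated interval from randomisation in both arms, whether or not the modules are finished. Waitlist participants begin CBT-I straight after this assessment, so its date also sets their treatment start. The trial team must settle which date applied and state it consistently.

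Recruitment is complete, so the practical part concerns reporting and analysis:

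1. Report actual days from randomisation to post-intervention assessment by arm (median, range and number missing).
2. Add one sensitivity analysis that either uses actual assessment time in the mixed model or restricts to a common window. Under the text reading with full use of the windows, the arms overlap only in weeks 7 to 8 from baseline, so a model adjustment relies on that overlap. Assessment time in the CBT-I arm also partly reflects adherence. Both are reasons to keep this as a sensitivity analysis and not the primary one.

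The cost is a wording correction and a little extra analysis. Assessments were completed in the app, so dates should exist, although the protocol does not say so. The drawback of a fixed date is that some slow completers are assessed before finishing all modules. The sample size does not change.
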